### Data Collection Methods

Demographic characteristics, full medical history, and dialysis-related parameters of study participants will be recorded on purpose-built data-collecting sheets (Multimedia Appendix 2). The study design diagram of the chronological sequence of the echocardiographic evaluations is presented in Figure 1. SPIRIT (Standard Protocol Items: Recommendations for Interventional Trial) reporting guidelines [17] have been used (Multimedia Appendix 3). Concomitant care and interventions during the HD session will be left to the attending nephrologist.

**Figure 1 figure1:**
[figure not shown]
Time sequence of the echocardiography evaluation. HD: hemodialysis.

### Echocardiography

2D and Doppler echocardiogram will be acquired by a skilled sonographer before and immediately after the HD session. Care will be taken in acquiring 2D apical views (4-chamber, 2-chamber, and long-axis views) aiming for the best visualization of the LV endocardial border. Images will be saved on digital media storage devices and analyzed offline at the echocardiographic core laboratory of our institution.

Echocardiographic images will be analyzed offline using dedicated software based on a mathematical model [18] (QStrain, Medis BV). The LV end-diastolic and end-systolic volumes and ejection fraction will be determined from the modified biplane Simpson method. Left atrial volume will be calculated using the biplane area-length method. LV volume and mass and left atrial volume will be subsequently indexed by body surface area. The peak early filling (E wave), the late diastolic (A wave) velocities, and the deceleration time will be assessed from the transmitral flow. The peak systolic (s’), early diastolic (e’), and late diastolic (a’) mitral annular velocities will be measured at the septal annulus using spectral Doppler.

LV volumes, estimated end-diastolic pressure, and brachial systolic and diastolic pressures will be used as input. The software reconstructs the pressure-volume (P-V) loop by determining the end-systolic pressure-volume relationship (ESPVR) and end-diastolic pressure-volume relationship (EDPVR) using the single-beat algorithms previously described in the literature [19]. Once the EDPVR and ESPVR are identified, the end-diastolic and end-systolic LV volumes and systolic and diastolic brachial pressures will be used to close the P-V loop. Finally, the P-V relation will be depicted for the entire cardiac cycle where each point of the curve is described as (Vt, Pt). In the P-V loop, the classic phases of the cardiac cycle are displayed: isovolumetric contraction, ejection, isovolumetric relaxation, and diastolic filling (Figure 2).

Based on this integrated P-V loop, the hemodynamic parameters to be calculated, both before and after the HD session, are listed in Textbox 3.

The pre- and posthemodialysis changes will be calculated and considered as potential prognostic indicators.

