### Hypothesis and Study Aims

The relevance of VAC as a parameter of hemodynamic optimization could be related to the fact that VAC is a parameter of cardiovascular efficiency whereas the classical hemodynamic parameters are exclusively parameters of cardiovascular efficacy.

With these concepts in mind, the main scientific questions and hypotheses of this project are:

What is the impact of HD on ventricular function?What is the impact of HD on ventricular and arterial elastance?What is the prognostic value of intradialytic VAC changes?

Accordingly, we sought to study patients with ESRD to assess (1) VAC parameters before and after the HD session, and (2) the value of VAC parameters in predicting adverse outcomes.

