### Expected Outcomes

Patients will be followed up for 18 months. Clinical variables and intradialytic changes in VAC parameters will be related to outcome events. The primary endpoint will be a composite of all causes of death, nonfatal myocardial infarction, and hospitalization due to worsening heart failure. Based on previous studies, we expect a mortality rate of around 10% per year [13], an incidence of acute myocardial infarction of 3.9 per 1000 patients per year [14], and an incidence of hospitalization due to worsening heart failure of 5.8 per 100 persons per year [15].

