### Statistical Analyses

Statistical analysis will be performed with Statistical Package Stata (StataCorp) and R-studio (Posit). All continuous variables will be presented as mean (SD) or median (IQR) based on their distribution. Paired comparisons of continuous variables will be performed with a 2-tailed paired Student *t* test or Wilcoxon test, when appropriate. Paired comparisons of categorical variables will be conducted with the McNemar test. Event-free survival for each of the echocardiographic and VAC parameters will be assessed using Kaplan-Meier analysis and compared with a log-rank test, where each index will be dichotomized according to the median of its distribution. The prognostic value will be determined using the Cox proportional hazards model. Differences will be considered statistically significant when *P*<.05. Interclass correlation coefficients (ICC) will be calculated to assess the inter- and intraobserver agreement of P-V loop measurements.

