Sasso et al [33] evaluated 15 patients on HD. They concluded that HD influences both Ees and Ea/Ees ratio acutely, although this effect seems due only to the acute reduction in preload and blood pressure, without any clinically significant effect on intrinsic LV contractility and VAC. In a study on 234 HD patients, Obokata et al [34] found that Ea/Ees ratio was independently associated with adverse outcomes, providing an incremental prognostic value over the clinical score and left ventricular ejection fraction. Recently, Zuo et al [35] used an approach similar to ours (pre- and posthemodialysis assessment of VAC). They concluded that VAC is a reliable index for stratifying the risk of cardiovascular diseases in HD patients.

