### Strengths and Limitations

The approach we are planning to use in this study allows a noninvasive assessment of the cardiovascular efficiency and the changes induced by volume changes during HD in patients with ESRD. The endocardial borders, evaluated by echocardiographic speckle tracking, can be used directly as input to the present model to provide a noninvasive assessment of VAC. Using standard echocardiographic images and advanced image analysis, we will be able to evaluate the heart-arterial system interaction from the VAC. We believe that, using this approach, a comprehensive analysis of the hemodynamic effects of volume changes induced by HD will be feasible. This will allow a better understanding of the pathophysiological changes induced by HD, with the potential of tailoring the optimal dialysis modalities and identifying those patients who are at higher risk of LV remodeling and future cardiovascular events.

Some challenges of this approach can be anticipated. First, echocardiographic image quality may affect proper visualization and tracking of the LV endocardial border. Second, a low frame rate can hamper the temporal resolution of the method. Finally, inter- and intraobserver reliability should be high to exclude changes due to variability.

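### The only fully specified prognostic test of the intradialytic VAC change is unadjusted for pre-HD VAC; the conclusion should rest on a Cox model with both

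*Protocol article*

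**What the plan says.** Three places in the protocol article make the change itself a predictor. The third question under Hypothesis and Study Aims is "What is the prognostic value of intradialytic VAC changes". Expected Outcomes states: "Clinical variables and intradialytic changes in VAC parameters will be related to outcome events". The Echocardiography section, after listing the parameters from the pressure-volume loop, adds: "The pre- and posthemodialysis changes will be calculated and considered as potential prognostic indicators".

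Statistical Analyses gives two tools. Event-free survival for the echocardiographic and VAC parameters is estimated by Kaplan-Meier and "compared with a log-rank test, where each index will be dichotomized according to the median of its distribution". Then: "The prognostic value will be determined using the Cox proportional hazards model". No covariates are listed for the Cox model, and it is not said to be univariable. The threshold is "Differences will be considered statistically significant when *P*<.05".

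Comparison to Previous Work cites a cohort of 234 HD patients in which "Ea/Ees ratio was independently associated with adverse outcomes". It does not say whether that ratio was measured before or after dialysis. On measurement error, Strengths and Limitations says "inter- and intraobserver reliability should be high to exclude changes due to variability", and Statistical Analyses plans inter- and intraobserver ICCs of the pressure-volume loop measurements.

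**The concern.** A change score contains its own starting value with a minus sign. Unless the post-HD values are clearly more spread out than the pre-HD values, patients with a high pre-HD Ea/Ees tend to show the larger falls. If the pre-HD level carries risk, the change inherits an association with outcome even when it adds nothing, and the sign is reversed: a rise in VAC during HD looks protective because it tends to follow a low starting value. A log-rank test on a median split of the change cannot separate the two explanations.

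The third research question asks about the change, not the level, and the abstract's conclusion links the assessment to tailoring volume removal. A positive result that only restates the pre-HD level would answer a different question. The planned ICCs do not settle this, because a high ICC for a single measurement does not show that the difference of two measurements is reliable.

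**Working it through.** **Inputs from the protocol article.** The sample size reproduces: 1.96² × 0.3 × 0.7 / 0.05² = 322.69, rounded up to 323. The annual rates in Expected Outcomes sum to 0.10 + 0.0039 + 0.058 = 0.1619. Over 18 months this gives 1 - exp(-0.1619 × 1.5) = 21.6%, and 323 × 0.216 is about 70 events. The 30% incidence in Sample Size would give about 97.

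**Inputs assumed.** The documents give neither the pre-post correlation r nor a hazard ratio for VAC. The ranges used are r = 0.5, 0.7, 0.9 and a hazard ratio (HR) of 1.3 to 2.0 per SD of pre-HD VAC, with equal pre and post variances and two-sided tests.

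**Step 1: correlation of change with the starting value.** With equal variances, corr(change, pre) = -√((1 - r)/2), which is -0.50, -0.39 and -0.22 at r = 0.5, 0.7 and 0.9.

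**Step 2: the induced hazard ratio.** If the hazard depends on pre-HD VAC only, the log hazard ratio per SD of change is roughly ln(HR) × corr(change, pre). At HR 1.5 and r = 0.7 this is exp(0.405 × -0.387) = 0.855; simulation gave 0.859.

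**Step 3: how often a change effect is declared when there is none.** Simulation with 323 patients, 18 months, hazard driven by pre-HD VAC alone at HR 1.5 per SD, about 70 events and 1000 runs per cell:

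| r | Log-rank, median split of change | Cox, change alone | Cox, change + pre-HD |
|---|---|---|---|
| 0.5 | 24.8% | 36.9% | 4.1% |
| 0.7 | 17.2% | 23.2% | 4.7% |
| 0.9 | 9.0% | 10.7% | 5.3% |

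A second simulation gave about 25%, 16% and 9% for the log-rank test. The simulation error at a true 5% is √(0.05 × 0.95 / 1000) = 0.7 percentage points. Over HR 1.3 to 2.0 the log-rank figure runs from 6% to 56% with about 70 events, and from 7.5% to 67% with about 97. At HR 1.0 all three tests hold about 5%.

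**Step 4: where the inflation disappears.** With equal variances, cov(post - pre, post + pre) = var(post) - var(pre) = 0. If the average of pre and post drives risk, the change is uncorrelated with it and nothing is induced. A simulation of pre and post as noisy readings of one stable VAC that drives the hazard (r = 0.7, HR 1.5 and 2.0) agrees. The log-rank test of change rejected in 5.6% and 6.3%, and Cox on change alone in 4.7% and 5.3%. In that same setting, the change adjusted for pre-HD VAC rejected in 22.1% and 48.9%.

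**Step 5: what the adjusted coefficient means.** b₁·pre + b₂·(post - pre) = (b₁ - b₂)·pre + b₂·post. The coefficient of change given pre-HD is the coefficient of post-HD given pre-HD. When pre-HD VAC is measured with error, post-HD VAC carries further information on the underlying level, so b₂ can be non-null with no effect of HD.

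**Step 6: reliability of the difference.** With equal variances it is (ICC - r)/(1 - r). At r = 0.7, an assumed ICC of 0.90 gives 0.20/0.30 = 0.67, and 0.85 gives 0.15/0.30 = 0.50.

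**The case against.** The strongest reply is that the protocol assigns prognostic value to the Cox model and does not say what is in it. A reader might infer that the change is analysed throughout without regard to the pre-HD value. The documents do not support that: the covariate list is simply not given, and a condensed article may leave it to an analysis plan that is not shown. That silence is not an error. What stands is narrower. The only test specified far enough to be carried out is the median-split log-rank test, and it is unconditional by construction. That section speaks of echocardiographic and VAC parameters and does not name change scores, so applying the test to change is an inference, though a natural one given the other three sections.

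Second, the cited cohort does not show that the pre-HD value specifically carries risk, because the timing of its measurement is not stated. Step 4 shows that the inflation depends on this. It also depends on the variances: at r = 0.7 and a post/pre SD ratio k, corr(change, pre) = (rk - 1)/√(1 + k² - 2rk). This is -0.61, -0.39 and -0.18 at k = 0.8, 1.0 and 1.2, and zero at k = 1/0.7 = 1.43. Both points stand as limits on the size.

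Third, adjustment is not a cure-all. If pre and post are noisy readings of one stable value, the adjusted term is the one that misleads. That case supposes no real individual response to HD, whereas the protocol treats HD as a real hemodynamic disturbance. It limits how the adjusted coefficient may be read, but it does not make the unadjusted test informative about change beyond level.

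**Conclusion.** The point holds in a limited form. For a named research question, the one fully specified test cannot distinguish a prognostic change from a prognostic starting level. If pre-HD VAC carries risk at HR 1.5 per SD, variances are equal and about 70 events occur, that test rejects in about 25%, 16-17% and 9% of studies at r = 0.5, 0.7 and 0.9, against a nominal 5%, and the apparent effect has the opposite sign to that of the level. The inflation is material at moderate correlation, small near 0.9, and absent if the average of pre and post drives risk.

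Two stronger inferences are not supported. The larger rejection rates for Cox on change alone (37%, 23% and 11%) belong to a model the protocol does not specify. Nor does adding the pre-HD value restore 5% in general; it does so when observed pre-HD VAC is what drives the hazard.

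The point does not touch the paired pre-post comparison or the sample size, which rests on the precision of an incidence.

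**What to change.** State in Statistical Analyses that, for each change index, the Cox model contains the continuous pre-HD value together with the change (equivalently, the post-HD value), and that the answer to the third research question rests on this model. Label the median-split log-rank test of change as descriptive. State that the adjusted coefficient is read as the added prognostic value of the post-HD measurement and not as proof of an HD-induced effect, because measurement error in pre-HD VAC can also make it non-null.

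Optionally, report from the planned repeat reads the ICC of the pre-to-post difference in Ea/Ees beside the ICCs of the single measurements, to support that reading.

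The cost is one extra covariate per model; all measurements are already planned. The interval for change widens by a factor of about √(2/(1 + r)), from 1/(1 - corr²) with corr² = (1 - r)/2: roughly 15%, 8% and 3% at r = 0.5, 0.7 and 0.9.

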**Figure 2 figure2:**
[figure not shown]
(A) Schematic representation of a pressure-volume loop. (B) Example of pressure-volume loop loop derived from echocardiographic images in one representative subject. Ea: arterial elastance; EDPVR: end-diastolic pressure-volume relation; EDV: end-diastolic volume; Ees: left ventricular systolic elastance; ESPVR: end-systolic pressure-volume relation; ESV: end-systolic volume; PE: potential energy; PVA: pressure-volume area; SW: stroke work.

Parameters derived from the pressure-volume loop and collected for analysis.Left ventricular systolic elastance: reflecting ventricular contractility and represented by the slope of the end-systolic pressure/volume (P-V) relation.Arterial elastance: reflecting the effective arterial afterload and represented by the slope of the line connecting the end-diastolic volume on the volume axis to the end-systolic P-V point on the P-V loop.Ventricular-arterial coupling: calculated as the ratio between arterial elastance and left ventricular systolic elastance.Stroke work (SW): the external work performed by the myocardium to eject blood, computed as the area enclosed by the P-V loop.Potential energy: ventricular energy dissipated during isovolumetric contraction.Pressure-volume area: the total mechanical energy generated by the contraction of the left ventricle, equal to the sum of potential energy and SW.Work efficiency: the efficiency of the mechanical energy transfer from the ventricle to the arterial tree, expressed as the ratio between SW and pressure-volume area.

### Data Management

This research involves a medical record review, image acquisition and analysis, and data analysis. Each participant will be assigned an ID number and all hard copy data collected or used during this study will be stored in a cabinet in the locked office of the study personnel. All electronic data will be stored on password-protected computers of the study personnel in their locked offices and the locked personnel building. Only essential research personnel will have access to any of these patient files.

### Statistical Analyses

Statistical analysis will be performed with Statistical Package Stata (StataCorp) and R-studio (Posit). All continuous variables will be presented as mean (SD) or median (IQR) based on their distribution. Paired comparisons of continuous variables will be performed with a 2-tailed paired Student *t* test or Wilcoxon test, when appropriate. Paired comparisons of categorical variables will be conducted with the McNemar test. Event-free survival for each of the echocardiographic and VAC parameters will be assessed using Kaplan-Meier analysis and compared with a log-rank test, where each index will be dichotomized according to the median of its distribution. The prognostic value will be determined using the Cox proportional hazards model. Differences will be considered statistically significant when *P*<.05. Interclass correlation coefficients (ICC) will be calculated to assess the inter- and intraobserver agreement of P-V loop measurements.

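### Every echocardiographic and VAC parameter is tested against outcome at an unadjusted P<.05, and the study's own prognostic question (intradialytic change in Ea/Ees) is not made the lead test

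*Protocol article*

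**What the plan says.** Statistical Analyses sets the rule for the outcome comparisons: "Event-free survival for each of the echocardiographic and VAC parameters will be assessed using Kaplan-Meier analysis and compared with a log-rank test". Patients are grouped for each of these tests by whether they lie above or below the sample median. The section then adds "The prognostic value will be determined using the Cox proportional hazards model", without naming an index or covariates, and closes with a single threshold: "Differences will be considered statistically significant when *P*<.05". It does not rank the indices, adjust the level or label any comparison exploratory.

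The indices are described elsewhere in Methods. Textbox 3 ("Parameters derived from the pressure-volume loop and collected for analysis") lists seven. The Echocardiography section says that "the hemodynamic parameters to be calculated, both before and after the HD session, are listed in Textbox 3", and that pre/post changes will be examined for prognostic use. The same section names about eleven conventional measures.

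The aims are narrower. Hypothesis and Study Aims asks about the prognostic value of VAC changes during dialysis, and Principal Findings in the Discussion repeats this. The Abstract defines VAC as one ratio, Ea/Ees. However, the Abstract's secondary objective and the Expected Outcomes section both widen the target to VAC parameters in the plural.

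**The concern.** Read together, the log-rank sentence and the threshold sentence give every listed index its own 5% test against the composite endpoint. With many indices, a nominally significant one can be expected fairly often by chance alone. Nothing in the section stops such an index from being reported as the prognostic finding when the change in Ea/Ees is itself null.

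The indices are also not separate pieces of evidence. By the definitions in Textbox 3, VAC is Ea divided by Ees, pressure-volume area is stroke work plus potential energy, and work efficiency is stroke work divided by pressure-volume area. Several of them moving together would look like confirmation but would largely be the same information.

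The stakes go beyond description. The Conclusions of the Abstract and the Strengths and Limitations section hope to use the results to guide fluid removal and to identify higher-risk patients.

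**Working it through.** **The plan's own figure.** The article states no number of tests and no overall error rate. Its sample size does reproduce: 1.96² × 0.3 × 0.7 / 0.05² = 322.7, rounded up to 323.

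**Inputs.**
- Level: 0.05 per test (Statistical Analyses). Two-sidedness is stated only for the paired comparison ("2-tailed paired Student *t* test or Wilcoxon test, when appropriate"); I take the log-rank tests as two-sided.
- Loop indices, 7 (Textbox 3): Ees, Ea, VAC, stroke work, potential energy, pressure-volume area, work efficiency.
- Conventional indices, about 11 by count (Echocardiography): end-diastolic and end-systolic volume, ejection fraction, LV mass, left atrial volume, E, A, deceleration time, s', e', a'. The total is 7 + 11 = 18.
- Events (Expected Outcomes): the yearly rates sum to 0.10 + 0.0039 + 0.058 = 0.1619. Over 18 months, 1 − exp(−1.5 × 0.1619) = 21.6%, or about 70 of 323. The 30% planning incidence would give about 97 (0.30 × 323). The event count is used only to run the simulation and does not enter the independence formula.

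**Formula.** If no index is prognostic and the m tests are independent, P(at least one false positive) = 1 − 0.95^m, and the expected number of false positives is 0.05 × m. Correlation lowers the probability but leaves the expected number unchanged.

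**Simulation.** To allow for linked indices, the same probability was simulated with no index prognostic: 323 patients, exponential event times at 0.1619 per year, 18 months of follow-up, median-split log-rank tests and 3,000 runs for each setting. The loop indices were built from shared volumes and pressures, with pre/post correlation of 0.5, 0.7 or 0.85. These distributions and correlations are assumptions.

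| Tests against outcome | m | Independent | Expected false positives | Simulated |
|---|---|---|---|---|
| Change in Ea/Ees only | 1 | 5.0% | 0.05 | 4.8–5.7% |
| 7 loop indices, once each (as changes) | 7 | 30.2% | 0.35 | 23–25% |
| 18 indices, once each | 18 | 60.3% | 0.90 | 52–54% |
| 7 loop indices in three forms | 21 | 65.9% | 1.05 | 50–53% |
| 18 indices in three forms | 54 | 93.7% | 2.70 | 86–89% |

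The plainest reading of the log-rank sentence, each listed parameter tested once, is the 18-index row. The narrowest reading, loop-index changes only, is the 7-index row.

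**Limits of the simulation.** It treats the Doppler, left atrial and LV mass measures as independent, so real correlation would lower the 18- and 54-test figures somewhat. It does not count the Cox tests, which would raise all of them.

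**The case against.** The strongest reply is that this is a condensed article about an observational cohort in which prognosis is the secondary objective. Test hierarchy and multiplicity are commonly left to an analysis plan that is not shown. That stands for anything the article merely omits. Here, though, the article states a rule: which indices are tested, how, and at what threshold. Following that rule as written produces the inflation.

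A second reply is that prognostic value is assigned to the Cox model, so the log-rank tests are only a screen. This stands in part. But the Cox sentence names no index, the same threshold covers both, and nothing says that a significant log-rank result would go unreported or be treated as provisional.

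A third is that the figures assume no index is prognostic, while the article itself cites a 234-patient hemodialysis study in which Ea/Ees was independently associated with adverse outcomes. That is fair, and the percentages are conditional on that assumption. It is also a reason to protect the Ea/Ees question instead of leaving it as one test among many.

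Two stronger readings are tempting and should not be adopted:
- A reader might infer that all 18 indices will be tested before, after and as change, making a false finding very likely. The document says that the loop indices are calculated at both times and that changes are candidate predictors. It does not say that every index enters the outcome tests in all three forms.
- A reader might infer that the study has no leading index at all. The aims and the Discussion do point to the dialysis-induced VAC change. What is missing is its transfer into the analysis rule.

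**Conclusion.** The point holds as a defect in a stated rule. One unadjusted threshold covers every echocardiographic and VAC parameter, and the study's own question about change in Ea/Ees has no protected place in it. With no truly prognostic index, the chance of at least one false finding is about 23–30% for the 7 loop indices tested once each and about 52–60% for 18 indices tested once each, against the nominal 5%. The 86–94% range belongs only to a 54-test grid that the document does not set out.

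These sizes rest on the count of about 11 conventional indices, on two-sided log-rank tests, on no index being prognostic and, for the lower ends, on the assumed correlations. The direction does not depend on them: even the narrowest simulated reading is between four and five times the nominal level. This should be changed, but it does not undermine the study's design or data.

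**What to change.** In Statistical Analyses, name one lead prognostic test at two-sided 0.05. A natural choice from the stated aims is a Cox model for the intradialytic change in Ea/Ees, given its pre-dialysis value. Named in advance, a single test keeps the false-positive risk at 5%.

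State that all other indices are exploratory and will be reported with hazard ratios and 95% confidence intervals. False-discovery-rate control across them is optional. Add that algebraically linked indices (VAC, pressure-volume area, work efficiency) will not be counted as independent confirmation. If all indices were to stay confirmatory instead, a Bonferroni level would be 0.05/7 = 0.0071 for the loop indices once each, or 0.05/18 = 0.0028 for all 18 once each.

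The cost is a change of wording and the loss of nominal significance for the other indices. No extra data are needed. The article reports 32 participants recruited by March 18, 2025 and schedules outcome analysis for January to June 2026, so on that timetable the lead test could be fixed before outcomes are analysed.

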### Ventriculo-Arterial Coupling

The concept that the cardiovascular system works better when the heart and the arterial system are coupled has been well demonstrated [5-7]. When the heart pumps blood into the vascular tree at a rate and volume that matches the capability of the arterial system to receive it, both cardiovascular performance and its associated cardiac energetics are optimal [8]. A contractility or arterial tone that is too high or too low decouples these processes and can lead to cardiac failure independent of myocardial ischemia or the toxic effects of sepsis and related systemic disease processes. This optimization means that the LV workload and the arterial system optimally match when the LV ejects the blood into the arterial system and is quantified by ventriculo-arterial coupling (VAC) parameters. This process is optimized without excessive changes in LV pressure, and the mechanical energy of LV ejection is completely transferred from the ventricle to the arterial system [9].

VAC can be defined as the ratio of the arterial elastance (Ea) to the ventricular elastance (Ees). This ratio was first proposed by Suga and Sagawa [10] as a method to evaluate the mechanical efficiency of the cardiovascular system and the interaction between cardiac performance and vascular function. The Ea/Ees ratio has been consistently demonstrated to be a reliable and effective measure of cardiovascular performance [11]. The balance between myocardial oxygen consumption and the mechanical energy required to perform this work appears to be optimal when the heart and the peripheral vascular system are coupled (ie, the Ea/Es is near unity). In this case, the LV provides an adequate stroke volume with the lowest possible energetic consumption [12]. Thus, VAC is an effective index of the mechanical performance of the LV and the dynamic modulation of the cardiovascular system.

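### Testing every index by a median-split log-rank comparison loses about 36% of the information for a roughly normal index, and the cut has no link to the Ea/Ees optimum near 1

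*Protocol article*

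**What the plan says.** Three statements in Statistical Analyses matter here. The first sets the survival comparison: "Event-free survival for each of the echocardiographic and VAC parameters will be assessed using Kaplan-Meier analysis and compared with a log-rank test", with the rule that "each index will be dichotomized according to the median of its distribution". The second follows directly: "The prognostic value will be determined using the Cox proportional hazards model". It does not say whether an index enters that model as continuous, split or non-linear. The third is the general threshold: "Differences will be considered statistically significant when *P*<.05". The log-rank comparisons are therefore tests and not only a way of drawing curves.

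The Echocardiography section adds the change scores to the candidate predictors: "The pre- and posthemodialysis changes will be calculated and considered as potential prognostic indicators".

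The rationale is in the Introduction, under Ventriculo-Arterial Coupling. Of the two components of the ratio it says: "A contractility or arterial tone that is too high or too low decouples these processes". Of the ratio itself it says that the energy balance appears best when "the Ea/Es is near unity". No cut-point tied to unity is given, and no non-monotone form.

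**The concern.** Two separate problems arise from the same rule.

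The first is efficiency. Splitting at the median treats a patient just above the median like one far above it. If risk changes steadily with the index, that discards information, and the expected number of events leaves little to spare.

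The second is shape. If coupling is best near a ratio of 1, departures in either direction may carry risk. A high-versus-low contrast can then put some at-risk patients in each group, so that they partly cancel. The cut is also placed wherever the sample median happens to fall, which need not be near 1.

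At stake is the secondary objective, the prognostic value of the VAC parameters. A non-significant log-rank result could be read as absence of prognostic value when it reflects the way the index was cut.

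**Working it through.** **Inputs from the article.** N = 323. The assumed incidence is 30%, with margin 0.05 and z = 1.96 (Sample Size). Expected rates per year are death 0.10, myocardial infarction 0.0039 and heart-failure hospitalization 0.058, with 18 months of follow-up (Expected Outcomes). The threshold is 0.05, taken here as two-sided.

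**Inputs that are assumptions.** The hazard ratios per SD, a normally distributed index, and the position of the optimum relative to the median. The article gives no median or SD for Ea/Ees.

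**The plan's own figure.** 1.96² × 0.3 × 0.7 / 0.05² = 322.7, rounded up to 323. It reproduces. It is a precision calculation for an incidence and does not depend on how the indices are analysed.

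**Expected events.**
- From the rates: 0.10 + 0.0039 + 0.058 = 0.1619 per year, and 1 − exp(−1.5 × 0.1619) = 0.2156. Then 323 × 0.2156 = 69.6, about 70. This adds the components as if they did not overlap.
- From the 30%: 323 × 0.30 = 96.9, about 97.

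**Information kept by a median split** (normal index, log-linear hazard): 2/π = 0.637. The loss is 36.3%, and the events needed rise by π/2 = 1.57.

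**Power.** Φ(√(D·V) × ln HR − 1.96), with D events, V = 1 for a continuous term and V = 2/π for the split. At HR 1.4, ln HR = 0.3365:
- D = 69.6, continuous: 8.345 × 0.3365 − 1.96 = 0.85, so 80%.
- D = 69.6, split: 6.658 × 0.3365 − 1.96 = 0.28, so 61%.

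| HR per SD | 70 events: continuous | 70: split | 97 events: continuous | 97: split |
|---|---|---|---|---|
| 1.3 | 59% | 42% | 73% | 54% |
| 1.4 | 80% | 61% | 91% | 75% |
| 1.5 | 92% | 77% | 98% | 89% |

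Events for 80% power at HR 1.4: (1.96 + 0.8416)² / 0.3365² = 69.3, so 70 for the continuous term. Multiplying by 1.57 gives 109 for the split.

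**Simulation check** (N = 323, 3000 replicates, Cox score tests). At HR 1.4 per SD the split has 58.5% power and the continuous term 79.6% with 70 events, or 74.1% and 90.5% with 97. Rejection under the null is 5.0% to 5.7%.

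**Two-sided departure.** The hazard is assumed to double for each SD away from an optimum, in either direction, with 70 events:

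| Distance of optimum from median | Split | Linear Cox term | Linear plus quadratic Cox |
|---|---|---|---|
| 0 | 5% | 11% | 94% |
| 0.25 SD | 26% | 34% | 95% |
| 0.5 SD | 67% | 73% | 98% |
| 1 SD | 96% | 99% | 99.5% |

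A second simulation used a different assumed curve (hazard × 1.35 per squared SD, 1000 cohorts, about 70 events) and a 3-knot spline. With the optimum at the median, power was 5% for the split, 12% linear and 90% spline. With the optimum 0.5 SD away it was 53%, 74% and 96%.

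**The case against.** The strongest reply is that prognostic value is assigned to the Cox model, in the sentence right after the split is described. The split is tied to the Kaplan-Meier and log-rank comparison, and nothing says that the Cox model uses dichotomised indices. A condensed article may leave the covariate form to a statistical analysis plan. This stands. A reader might infer that the whole prognostic analysis loses a third of its information, and the document does not show that. What remains is that the median split is the only form the article states for any index, and that it is attached to a test at P<.05.

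A reader might also infer that the split cannot detect the relation the authors have in mind. That goes too far in two ways. The wording about too high or too low concerns contractility or arterial tone; for the ratio the article says only that it is best near 1, so two-sided risk for Ea/Ees is a reasonable inference and not a stated hypothesis. And the split falls to the false-positive level only when the optimum sits at the sample median with symmetric risk. If most patients lie on one side of 1, it detects the gradient.

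In that symmetric case a linear Cox term does little better (11% to 12%). The fault there is a monotone form, not dichotomisation as such.

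The unity argument applies to the level of Ea/Ees. It does not carry over to pre/post changes, stroke work or the other indices. For those only the efficiency argument holds.

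**Conclusion.** The point holds for the log-rank analysis. The stated rule loses about 36% of the information on an index that is roughly normal with a log-linear effect. At an assumed HR of 1.4 per SD, that is about 60% power against 80% with 70 events, or 75% against 91% with 97. The loss would differ for a skewed index or a true threshold effect.

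For the Ea/Ees level, a cut at the sample median is also poorly matched to an optimum near 1. How much that costs cannot be fixed from the document, because it depends on how far the median lies from 1: the assumed curves give the split anything from 5% to 96% power. A non-linear term had the highest power at every distance examined.

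The document does not support a prediction that the study will wrongly report no prognostic value, because the form of the Cox covariates is not given.

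**What to change.** In Statistical Analyses, state that prognostic conclusions rest on the Cox model, with each index and each pre/post change entered as a continuous variable. For the Ea/Ees level, pre-specify a non-linear term, for example a 3-knot restricted cubic spline of log(Ea/Ees) tested on 2 degrees of freedom. Keep the Kaplan-Meier curves as descriptive, and draw no conclusion from the median-split log-rank test.

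This needs no new data, only a change of wording and a few lines of code. The price is one extra degree of freedom for Ea/Ees. If its effect is truly linear (HR 1.4 per SD, about 70 events), the spline has about 67% power in simulation against 79% for a linear term, which is still above the 58% of the split.
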